## Introduction

### Sedentary: A public health issue

A less active or sedentary lifestyle is associated with higher mortality and the development of chronic pathologies including cancers (in particular colon, breast and endometrial cancer), type 2 diabetes, obesity, arterial hypertension, ischemic heart disease, osteoporosis [1–4]. Various studies indicate that the morbid processes associated with these pathologies and favored by sedentary behavior (SB) beginning in childhood or adolescence [5]. This period is conductive for the habit set up of the future adult. In particular, habits relating to physical activity (PA) practice, underlining the need to decrease the adoption of a sedentary lifestyle from an early age. According to Sedentary Behavior Research Network, SB is defined as any waking behavior characterized by an energy expenditure ≤1.5 metabolic equivalents (METs), while in a sitting, reclining or lying posture [6–8]. The sedentary lifestyle of children has commonly been measured by the time spent in front of a screen [9–11]. A large-scale study conducted in 2015–2017 in 25 European countries on school-aged children (6–9 years old), reported that a mean of 25.2% of children spent 2 to 3 hours per day in front of a screen and 14.6% more than 3 hours per day [12]. The common sense census survey of the US reported that 8 to 12 years old children spent 4.44 hours per day on average using screen media; 25% spent 2–4 hours, 26% spent 4–8 hours and 15% more than 8 hours each day using a screen media, respectively [13]. French studies showed that more than 50% of school-aged children (6–10 years) spent more than 3 hours a day in front of a screen (ESTEBAN study) [14], and their screen time (ScT) has increased of 20 minutes per day between 2007 and 2015 (INCA2 and INCA3 studies, respectively) [15, 16]. However, sedentary time (ST) longer than 2 hours a day (evaluated mainly by time spent in front of TV) has been associated with an unfavorable body composition, reduced physical condition, lower self-esteem, lower sociability and poorer academic achievement in children and adolescents (5–17 years) [17]. In this context, designing and testing effective interventions to decrease SB in school-aged children therefore appears today to be a major public health issue (listed in the priorities of the French National Nutrition and Health Program) [18].

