#### Children PA and SB objective assessment

Commonly used for objectively measuring PA, Triaxial GT3X+ accelerometers (ActiGraph,FL,USA) will be used to assess ST and different levels of PA (i.e. low physical activity (LPA), moderate physical activity (MPA) vigorous physical activity (VPA)) and moderate to vigorous physical activity (MVPA)) for children. The devices will be placed on the dominant wrist during 7 consecutive days, and 24 h per day. Nevertheless, children will have to remove it when they go to a water environment (e.g. bath time, shower, swimming…). Accelerometers will be initialized to record data at a sample frequency of 60 Hz using ActiLife software (V6.13.4 Full Edition, ActiGraph, FL, USA). Non-wear time will be defined using Choi’s et al., algorithm which consists of 60 min of 0 counts per minutes (cpm) with an allowance of 2 min of activity when it is placed between two 30 min windows of 0 cpm [69]. Validated wear time’s data will be downloaded and aggregated into 5s epochs and daily levels of ST and PA will be determined using Crouter’s et al., validated cut points [70].

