(i) Children’s sleep habits: Parents will be asked to report the average wake up time and bedtime of their children for the last seven days during weekdays and weekend days, out of the holidays. It will exclude the time spent in front of a screen before sleeping or after waking up. In addition, it will be asked to report the average time spent napping for the last seven days during weekdays and weekends following a six-point scale: 1 [No nap]; 2 [1–15 min]; 3 [15–30 min]; 4 [30–45 min]; 5 [45 min-1h]; 6 [more than 1h].(ii) Children’s SB: Parents will be asked to report their child’s sedentary habits, and more precisely, time spent in front of a screen, sitting activities or lying down activities, on the last seven days out of holidays. About ScT, parents will be asked to declare the time spent by their children: (i) watching TV (including TV, YouTube or other media platform, DVD, blue ray) during or out of mealtime, (ii) playing video games (including computers, games console, tablet or smartphone) without including standing games, and (iii) using a computer, tablet or smartphone for other activities (including homework, social media, SMS or internet surfing). All questions are scored following a nine-point scale: 1 [never]; 2 [1-15min]; 3 [15–30 min]; 4 [30 min-1h]; 5 [1h-2h]; 6 [2h-3h];7 [3-4h]; 8 [4h-5h]; 9 [more than 5h]. About other sedentary activities, parents will be asked to declare time spent sitting or lying down by their children without using a screen, such as doing their homework, reading a book or taking leisure time (e.g., board games, drawing, listening to music, etc.). All questions are scored following an eight-point scale: 1 [never]; 2 [1-15min]; 3 [15–30 min]; 4 [30 min-1h]; 5 [1h-2h]; 6 [2h-3h]; 7 [3h-4h]; 8 [more than 4h].(iii) Children’s PA habits: Parents will be asked to report the time spent by children in PA on a typical week, out of the holidays. This section is made of two tables, one refers to the leisure PA done in a sports club, and the other concerns the leisure PA done during the family time out of a sports club. Parents can declare several activities in the two categories; for each declared activity, they are asked to report: (i) the average time spent in the activity using a five-point scale (1 [less than 30 min]; 2 [30 min-1h]; 3 [1h-1h30]; 4 [1h30-2h]; 5 [more than 2h]); (ii) the week frequency using a five-point scale (1 [less than 1 time a week]; 2 [1 time a week]; 3 [twice a week]; 4 [3 times a week]; 5 [more than 3 times a week]); and (iii) intensity using a three-point scale (1 [light]; 2 [moderate]; 3 [high]).(iv) Children’s travel habits: Parents will be asked to report sedentary and active transport habits of their children. This section is made of two tables. The first table concerns time spent between house and school and the second table includes the time spent to go to other activities/locations. Each table is divided into two ways of transport, motorized (e.g., car, bus, train, etc.) and non-motorized (e.g., walk, bike, skateboard, etc.). The average transport time during the last seven days (out of holidays) is requested to use a nine-point scale: 1 [never]; 2 [1–15 min]; 3 [15–30 min]; 4 [30 min-45 min]; 5 [45 min-1h]; 6 [1h-1h30];7 [1h30-2h]; 8 [2h-2h30]; 9 [2h30-3h].(v) Family social characteristics: Characteristics of respondents to survey (father, mother, other…) are asked, including the birthday of each parent, and some information about their social situation: homeowner (yes/no), number of children in care, if children have TV in their room (yes/no), the socio-professional category and the study level of both parents.

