### Statistical considerations

#### Sample size calculation

In a French study measuring ST with Actigraph GT3X accelerometers, children aged 7 to 10 accumulated 583 minutes on average (standard deviation: 57 min) of ST per day [76]. We will aim with the CIPRES intervention to reduce by 30 minutes per day the ST in the target population. To evaluate the number of subjects needed, we will choose α risk equal to 5% and β risk equal to 10% (power = 90%). Without considering clusters, showing a decrease of 30 minutes of ST per day between pre- and post-intervention will require to include 92 children per group (taking into account a correlation of 0.4 between baseline and follow-up measures). Randomization by cluster requires taking into account inflation factor of our sample size because of the homogeneity of the conditions within each cluster: 1+(m(1+cv^2^)-1)r (m being the average number of subjects per cluster, cv a coefficient of variation equal to the ratio between the standard deviation of the size of the clusters per m, and r being the intraclass correlation coefficient). In our study, the cluster is a municipality. With a potential average of 150 children included per municipality, a coefficient of variation at 0.5, and a rho coefficient set at 0.01 according to databases of intraclass correlation coefficients [77] and a recent French study [78], the inflation factor is equal to 2.87. The number of subjects needed to be able to show a difference of 30 minutes per day in ST is estimated at 527 children. Taking into account a potential rate of 25% of lost-to-seen over time, the number of subjects to include in the CIPRES study amounts to 700 children (i.e., 350 in the intervention group and 350 in the control group), corresponding to approximately 14 classes per group (i.e., approximately 7 schools per group).

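### As written, the accelerometer processing scores part of night-time sleep as sedentary time, so the primary outcome does not match the protocol's waking definition or its planning figures

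*Protocol article*

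**What the plan says.** All references are to the protocol article.

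- **Construct.** The Introduction (Sedentary: A public health issue) adopts a research-network definition: "SB is defined as any waking behavior characterized by an energy expenditure" of at most 1.5 METs, in a sitting, reclining or lying posture.
- **Primary outcome.** Effectiveness assessment names accelerometer-measured ST over 7 days, weekdays and weekend days included.
- **Wear.** Children PA and SB objective assessment states: "The devices will be placed on the dominant wrist during 7 consecutive days, and 24 h per day". The only planned removal is for water.
- **Processing.** The same section gives the sampling rate (60 Hz), the software version and a non-wear rule (60 min of zero counts, with a 2-min allowance). It continues: "Validated wear time’s data will be downloaded and aggregated into 5s epochs and daily levels of ST and PA will be determined", using published cut points.
- **Sleep information.** In Evaluation of children behavior by their parents: "Parents will be asked to report the average wake up time and bedtime of their children for the last seven days". No use of these times in scoring the accelerometer is stated.
- **Planning figures.** Sample size calculation relies on a French study in which "children aged 7 to 10 accumulated 583 minutes on average (standard deviation: 57 min) of ST per day", and on a target reduction of 30 min/day.

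**The concern.** The processing runs from 24 h wear, through removal of long zero-count runs, to cut points applied to what is left. Nothing in it separates sleep from waking stillness. The article does not reproduce the cut-point values, but ST is the lowest-intensity band, so low-count sleep that survives the non-wear filter should fall mostly there.

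The non-wear rule does not solve this. A sleeping child who is motionless for an hour loses that hour as non-wear, while a child who moves a little keeps it as ST. The part of the night that enters the outcome therefore depends on movement during sleep, which has nothing to do with sedentary behaviour.

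What is at stake is the meaning of the primary estimate, and whether the planning mean and SD apply to the variable that will be analysed.

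**Working it through.** **1. The plan's own sample size.** Inputs from Sample size calculation: difference 30, SD 57, α 5% (taken as two-sided), power 90%, correlation 0.4, m = 150, cv = 0.5, ICC = 0.01, loss 25%.

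- Unadjusted n per group: 2 × [57 × (1.960 + 1.282)/30]² = 75.86.
- Change-score factor: 2 × (1 − 0.4) = 1.2, so 75.86 × 1.2 = 91.04, which rounds up to 92 (stated: 92).
- Inflation: 1 + (150 × 1.25 − 1) × 0.01 = 2.865 (stated: 2.87).
- Total: 184 × 2.865 = 527 (stated: 527).
- With loss: 527/0.75 = 703 (stated: 700).

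The plan's arithmetic reproduces. The point does not depend on an error in it.

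**2. Which variable do 583 and 57 describe?** 1440 − 583 = 857 min, or 14.3 h, outside ST each day. Sleep length is not given in the documents. Assume 9 to 10 h (540 to 600 min). If that sleep were inside the 583 min, waking ST would be 583 − 540 = 43 min at most, which is implausible for schoolchildren. The planning mean therefore reads as waking ST.

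**3. What the outcome would average if processed as written.** Assume 8 to 11 h of sleep, with 25% to 100% kept as wear and scored as ST. Both ranges are assumptions.

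- Low end: 583 + 0.25 × 480 = 703 min/day; sleep share 120/703 = 17%.
- High end: 583 + 660 = 1243 min/day; sleep share 660/1243 = 53%.

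The high end is a ceiling, because some still sleep would be dropped as non-wear. Even at the low end, 583 (SD 57) does not describe the outcome.

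**4. Illustration of power.** Let retained sleep add an independent between-child SD of s, with T0–T1 correlation ρ. Waking ST keeps correlation 0.4.

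- Change-score variance: V = 1.2 × 57² + 2(1 − ρ)s².
- Power: Φ(30/√(2V/92) − 1.96), on the plan's own basis of 92 effective children per group.
- With s = 0: V = 3898.8 and power is 0.90.

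| s (min) | Total SD = √(57² + s²) | Power, ρ = 0.4 | Power, ρ = 0.8 |
|---|---|---|---|
| 30 | 64.4 | 0.82 | 0.88 |
| 60 | 82.8 | 0.61 | 0.80 |
| 90 | 106.5 | 0.41 | 0.67 |

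Example, s = 60:

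- ρ = 0.4: V = 3898.8 + 1.2 × 3600 = 8218.8; 30/√(2 × 8218.8/92) = 2.24; power 0.61.
- ρ = 0.8: V = 3898.8 + 0.4 × 3600 = 5338.8; 30/√(2 × 5338.8/92) = 2.78; power 0.80.

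Neither s nor ρ for the sleep component is in the documents.

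**The case against.** The best answer is that this is an omission in a condensed article. Nowhere does the article say that sleep is counted. It also gives no minimum wear time or number of valid days, so its processing description may be incomplete, and the full protocol or analysis plan may contain a sleep step. The waking definition, the 583 min/day and the collection of bed and wake times all suggest that waking ST is the intended target. This stands to the extent that a reader should not infer that sleep certainly will be counted.

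It does not remove the point. The article fixes the sampling rate, non-wear rule, epoch and cut points, and says what is classified: validated wear time from a device worn day and night. Carried out as stated, that yields a different variable from the one defined and planned for.

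The objection is also right about size. The added SDs are assumed, and the planned model includes individual random effects, so a sleep component that is stable within a child largely cancels in the change from T0 to T1. That is why the ρ = 0.8 column belongs beside the ρ = 0.4 column.

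A reader might go further and infer a directional bias: less evening screen use lengthens sleep, and the extra sleep is scored as ST, hiding part of the benefit. The documents do not support this as a finding. They give no effect of the intervention on sleep, and both arms and both time points are processed alike. Like processing would not prevent such a bias if sleep did change in one arm, but that change is not shown and no figure can be put on it.

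**Conclusion.** The concern holds in this form: the stated processing would score an irregular part of night-time sleep as ST. That conflicts with the article's waking definition and with a planning mean and SD that are plausible only for waking ST. The conflict concerns the primary outcome and should be settled before outcome data are analysed.

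The conflict itself rests on the text. That retained sleep would score mostly as ST rests on how activity cut points treat low counts, and the reading of 583 min as waking time rests on an assumed sleep length. The power loss is illustrative only: from slight (88%) to severe (41%), depending on two quantities that the documents do not give. It would also be wrong to infer that the whole night enters the outcome, since the non-wear rule would drop part of it. The sample size of 700 needs no change on this account if the outcome is restricted to waking ST.

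**What to change.** Define the primary outcome explicitly as waking ST. Before non-wear detection and cut points are applied, identify the sleep window and remove it, using one pre-specified rule for both arms and for T0 and T1. Use device-based sleep detection on the 24 h recordings by default, with parent-reported bed and wake times as back-up. State the rule in the accelerometer section and make that section consistent with the definition in the Introduction and the planning figures in Sample size calculation. If the full protocol already contains such a rule, one sentence reporting it is enough.

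The cost is one extra processing step on data already being collected, plus some error in detecting sleep. Parent reports should not be the main source: questionnaire completion was 64% in the pilot (Feasibility study), and the times are averages, not nightly records.

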#### Children self-reported screen habits and school activities

A diary will assess children’s habits of screen use. Children will have to report their favorite screen (e.g., smartphone, TV, computer, video game or tablet), which one they use the most, if they watch screens in their bedroom, where they spend the most of the time in front of a screen (e.g. bedroom, kitchen, living room, outdoor, in a friend’s house) with who (e.g. family members or friends), and what kind of content (e.g. social media, movies/series, cartoons, video games or documentary). The diary will also allow children to report what PA type they do at school with their teacher, how long and how often as well as what kinds of activities they do during break time (e.g., board games, ball games, hopscotch, talking, catch me if you can or others).

#### Psychosocial variables in children

The TCM variables will be measured with two self-reported questionnaires administered to children in class including questions related to self-determined motivation, attitudes, norms (subjective and descriptive), perceived behavioral control and intentions. Each survey will be evaluated on its own scale.

The study will use a 15-item survey which was created to assess the motivational level for spending less time in front of a screen. Children will answer the questions, all starting with “I spend less time in front of screens because…”, using a five-point scale: 1 [not true]; 2 [a bit true]; 3 [quite true]; 4 [True]; 5 [very true]. The scale includes five motivational dimensions, each one being measured with three items: intrinsic motivation (e.g., “because I don’t like watching TV”), identified regulation (e.g., “because it’s important for my health”), introjected regulation (e.g.,”I feel guilty if I spent too much time in front of a screen”), external regulation (e.g. “to please my parents”), and amotivation (e.g.,”I don’t understand why we need to spend less time in front of the screens”). A Cronbach Alpha coefficient will be used to test the correlation between items from the same dimension.

The assessment of other psychosocial variables of the TCM (i.e., attitudes, norms (subjective and descriptive), perceived behavioral control and intentions) is based on current guidelines [71] and will be based on a 16-item survey using a four-point scale to respond: 1 [not at all]; 2 [not really]; 3 [yes, a bit]; 4 [yes, a lot]. Attitudes will be measured using 3 items (e.g., do you think that spending a lot of time in front of a screen will be boring?). Perceived behavioral control for children to decrease screen use in leisure time will be assessed using 3 items (e.g., do you feel able to easily find some activity to do without using screens?). To assess descriptive norms, the questionnaire will include 3 items (e.g., does your mother spend a lot of time in front of screens in her everyday life?). Subjective norms assessment will be based on 4 items (e.g., does your teacher want you to spend less time in front of screens?). Finally, intentions will be measured using 3 items (e.g., during the next week, will you want to spend less time in front of screens?).

#### Children quality of life

The French translated form of the kidscreen-10 questionnaire will be used to assess the quality of life in children. Kidscreen-10 is a validated self-reported health-related quality of life questionnaire for children and adolescents aged from 8 to 18 years, derived from the Kidscreen-27 itself derived from the Kidscreen-52 [72, 73]. It is made of ten questions using a five-point scale to respond: 1 [never]; 2 [sometimes]; 3 [often]; 4 [very often]; 5 [always] excepted for questions 1 and 9, which use another five-point scale to respond: 1 [not at all]; 2 [a little]; 3 [moderately]; 4 [a lot]; 5 [extremely].

#### Evaluation of children behavior by their parents

This study will use an adapted version of the SIT-Q-7d questionnaire that has been validated in adults [74]. This parent’s survey is a self-reported survey that quantifies their children’s behavior in the last 7 days regarding SB and PA across several domains covering the children’s daily life activities:

(i) Children’s sleep habits: Parents will be asked to report the average wake up time and bedtime of their children for the last seven days during weekdays and weekend days, out of the holidays. It will exclude the time spent in front of a screen before sleeping or after waking up. In addition, it will be asked to report the average time spent napping for the last seven days during weekdays and weekends following a six-point scale: 1 [No nap]; 2 [1–15 min]; 3 [15–30 min]; 4 [30–45 min]; 5 [45 min-1h]; 6 [more than 1h].(ii) Children’s SB: Parents will be asked to report their child’s sedentary habits, and more precisely, time spent in front of a screen, sitting activities or lying down activities, on the last seven days out of holidays. About ScT, parents will be asked to declare the time spent by their children: (i) watching TV (including TV, YouTube or other media platform, DVD, blue ray) during or out of mealtime, (ii) playing video games (including computers, games console, tablet or smartphone) without including standing games, and (iii) using a computer, tablet or smartphone for other activities (including homework, social media, SMS or internet surfing). All questions are scored following a nine-point scale: 1 [never]; 2 [1-15min]; 3 [15–30 min]; 4 [30 min-1h]; 5 [1h-2h]; 6 [2h-3h];7 [3-4h]; 8 [4h-5h]; 9 [more than 5h]. About other sedentary activities, parents will be asked to declare time spent sitting or lying down by their children without using a screen, such as doing their homework, reading a book or taking leisure time (e.g., board games, drawing, listening to music, etc.). All questions are scored following an eight-point scale: 1 [never]; 2 [1-15min]; 3 [15–30 min]; 4 [30 min-1h]; 5 [1h-2h]; 6 [2h-3h]; 7 [3h-4h]; 8 [more than 4h].(iii) Children’s PA habits: Parents will be asked to report the time spent by children in PA on a typical week, out of the holidays. This section is made of two tables, one refers to the leisure PA done in a sports club, and the other concerns the leisure PA done during the family time out of a sports club. Parents can declare several activities in the two categories; for each declared activity, they are asked to report: (i) the average time spent in the activity using a five-point scale (1 [less than 30 min]; 2 [30 min-1h]; 3 [1h-1h30]; 4 [1h30-2h]; 5 [more than 2h]); (ii) the week frequency using a five-point scale (1 [less than 1 time a week]; 2 [1 time a week]; 3 [twice a week]; 4 [3 times a week]; 5 [more than 3 times a week]); and (iii) intensity using a three-point scale (1 [light]; 2 [moderate]; 3 [high]).(iv) Children’s travel habits: Parents will be asked to report sedentary and active transport habits of their children. This section is made of two tables. The first table concerns time spent between house and school and the second table includes the time spent to go to other activities/locations. Each table is divided into two ways of transport, motorized (e.g., car, bus, train, etc.) and non-motorized (e.g., walk, bike, skateboard, etc.). The average transport time during the last seven days (out of holidays) is requested to use a nine-point scale: 1 [never]; 2 [1–15 min]; 3 [15–30 min]; 4 [30 min-45 min]; 5 [45 min-1h]; 6 [1h-1h30];7 [1h30-2h]; 8 [2h-2h30]; 9 [2h30-3h].(v) Family social characteristics: Characteristics of respondents to survey (father, mother, other…) are asked, including the birthday of each parent, and some information about their social situation: homeowner (yes/no), number of children in care, if children have TV in their room (yes/no), the socio-professional category and the study level of both parents.
